### Plans to give access to the full protocol, participant-level data and statistical code {31c}

The protocol will be registered at the Australia New Zealand Clinical Trials Registry (ANZCTR), where specifics not present in the current publication may be reviewed.

## Oversight and monitoring

### Composition of the coordinating centre and trial steering committee {5d}

The Principal Investigator, the research assistant/co-ordinator and at least one other Investigator (Internal Trial Monitoring Committee) will meet at least monthly to monitor the progress of the trial to discuss study progress and procedures, adverse events and any other issues,

### Composition of the data monitoring committee, its role and reporting structure {21a}

The Principal Investigator will act as the data manager for the trial. The research team will meet as above in lieu of an official Data Monitoring Committee. Direct access to the data will be granted to authorised representatives from the sponsor, host institution or ethics board for monitoring and/or audit to ensure compliance with regulations.

### Adverse event reporting and harms {22}

Participant safety will be ensured via standard institutional protocols. The use of the GNRB is established to be safe in pre-operative [53] and early post-operative patients [42], with no adverse events reported, and this will be expressed verbally to patients prior to participation. Adverse events are defined as medical occurrences that may or may not have a causal relationship with the surgical treatment administered. Any adverse events identified will be recorded and reviewed regularly by the Internal Trial Monitoring Committee. The Principal Investigator will determine causality. The number and type of adverse events (AEs) will be recorded up to 24 months. Any AEs will be noted on the REDCap database. These events will also be reviewed by the participants’ medical and surgical teams (who are not a part of the investigative team) as part of standard care.

Serious adverse events (SAE) are defined as any untoward and unexpected medical occurrence that results in death, is life-threatening, requires hospitalisation or prolongation of existing inpatients’ hospitalisation, results in persistent or significant disability or incapacity, is a congenital anomaly or birth defect, or is any other important medical condition which, although not included in the above, may require medical or surgical intervention to prevent one of the outcomes listed. All SAEs will be reported to the approving ethics board within 72 h of the investigators becoming aware of them. SAEs that may be expected as part of the surgical interventions and that do not need to be reported to the HREC are complications of anaesthesia or surgery (wound infection, bleeding or damage to adjacent structures such as nerves, tendons and blood vessels, delayed wound healing, and thromboembolic events, femoral or tibial fracture).

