##### Suture tape augmentation technique

Patients randomised to the SA arm will use the Tightrope 2 femoral cortical button, which has a single strand of Fibertape looped through the proximal Tightrope to be run alongside the graft to serve as an augment. The femoral button and graft will then be docked into the femoral tunnel, 5 mm short of the tunnel depth by shortening the adjustable loop in a similar fashion to the standard ACL reconstruction group. The tibial side of the graft is then cycled 15 times with maximal manual tension applied. Secondary tibial fixation of the suture tape will be performed before the tibial graft, with a 4.75-mm SwiveLock anchor in full extension. A guide pin was drilled 1.5 cm distal to the tibial tunnel to a depth of 20mm and overrreamed with a 3.4-mm diameter reamer and 4.75-mm tap. Ensuring the free ends of the Fibertape are separate from the tibial-sided graft sutures, a haemostat is then placed underneath the FiberTape limbs to ensure it is not tighter than the graft. The suture tape is then fixed with a 4.75-mm SwiveLock anchor with the knee in maximal knee extension. The graft will be tensioned at 0° of knee flexion with a proprietary “fish scale” tensioning device used to apply tension to the graft at 80N, and a posterior force on the tibia. The tibial side of the graft will then be secured with an interference screw (PEEK; Arthrex Inc.), with the suture tape running alongside the graft through the tibial tunnel, with tension on the graft only. The knee is then cycled through a range of motion to ensure the full range is present. In order to ensure greater tension on the graft than the tape, the femoral side of the graft is then re-tensioned to ensure fully docked within the femoral tunnel at 30° of knee flexion.

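### The SAE definition requires an event to be unexpected, yet the same section exempts expected SAEs from ethics reporting, so serious listed complications have no consistent classification

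*Protocol article*

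**What the plan says.** All in the Protocol article, under Adverse event reporting and harms {22} unless stated otherwise:

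- **Definition.** "Serious adverse events (SAE) are defined as any untoward and unexpected medical occurrence that results in death", is life-threatening, leads to hospitalisation, or meets one of the further criteria given.
- **Reporting rule.** "All SAEs will be reported to the approving ethics board within 72 h of the investigators becoming aware of them". This sentence carries no exception.
- **Exemption.** The next sentence introduces "SAEs that may be expected as part of the surgical interventions and that do not need to be reported to the HREC". It lists anaesthetic and surgical complications, among them wound infection and bleeding, and ends with "delayed wound healing, and thromboembolic events, femoral or tibial fracture".
- **Adverse events in general.** Any adverse event is recorded, by number and type, up to 24 months and reviewed by the Internal Trial Monitoring Committee. Expectedness is not a condition here.

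Elsewhere, Secondary outcomes makes complications and adverse events a recorded outcome. The statistical methods section {20a} compares complication rates between arms with Fisher's exact test. The Discussion hypothesises that complication profiles will be equivalent.

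**The concern.** Seriousness describes what an event does to the patient. Expectedness describes whether the event was foreseen, and normally decides only how quickly it must be reported. Here the two are joined in the definition, so a foreseen complication cannot be an SAE however severe it is. The section then speaks of expected SAEs as if they existed.

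Staff who follow the definition and staff who follow the exemption will classify the same event differently. An SAE count by arm would then depend on who did the classifying, and the events most likely to move in or out of it are the serious complications that this surgery is known to produce. The trial puts forward a hypothesis about complication profiles and has the research team meet "in lieu of an official Data Monitoring Committee", so the classification of serious harms should not be open to two readings.

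**Working it through.** No arithmetic applies: the point turns on wording and uses no sample size, power or event rate. I set the three sentences side by side and then follow one event through them. I take the approving ethics board and the HREC to be the same body.

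**Step 1: can the three sentences hold together?**

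1. Definition: SAE = meets a seriousness criterion AND unexpected.
2. Reporting rule: every SAE goes to the ethics board within 72 h.
3. Exemption: an SAE that is expected and listed does not go to the ethics board.

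By sentence 1, the class (SAE and expected) has no members, so sentence 3 exempts nothing. If sentence 3 is meant to exempt something, some SAEs must be expected. Sentence 1 is then wrong, and the unqualified *all* in sentence 2 is wrong too.

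**Step 2: follow one event.** Take a tibial fracture that needs hospitalisation. It meets a seriousness criterion and is on the list.

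| | Definition governs | Exemption governs |
|---|---|---|
| Is it an SAE? | No | Yes |
| In an SAE count? | No | Yes |
| Sent to the ethics board? | No, because it is not an SAE | No by the exemption; yes by the rule for all SAEs |
| In the adverse event record to 24 months? | Yes | Yes |
| Open to recording as a complication? | Yes | Yes |

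The last row rests on Secondary outcomes. Its list of complications does not name fracture, but it is worded as examples, so fracture is not excluded.

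**Step 3: serious events that are foreseen but not listed.** The definition does not tie *unexpected* to the exempt list. Suppose the bracketed list is read as closed, and consider a hospital admission for graft failure, which the Sample size section itself anticipates. If the definition governs, the event could be called expected, would then not be an SAE, and would not be reported. If seriousness alone governs, it is an SAE due at the ethics board within 72 h. For events of this kind the two readings differ in the report as well as in the label.

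**Step 4: what differs between the arms.** Under Suture tape augmentation technique, "Secondary tibial fixation of the suture tape will be performed before the tibial graft, with a 4.75-mm SwiveLock anchor in full extension", and "A guide pin was drilled 1.5 cm distal to the tibial tunnel". The section on graft fixation gives both arms an interference screw on the tibial side, and the standard technique describes no such anchor. Tibial fracture is on the exempt list. No section connects fracture with the anchor hole.

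**The case against.** The strongest reply is that the slip hardly changes conduct. Under either reading a listed complication is recorded and not sent to the ethics board, and the exemption can be read as qualifying the sentence before it. This stands for ethics-board reporting of listed events. It does not stand for the SAE count, which changes with the reading, or for foreseen events that are not listed (step 3).

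A second reply is that the protocol describes no between-arm SAE table. Its stated harms comparison is of complication rates, drawn from medical records, and does not use the SAE label. This also stands: the planned Fisher's exact test is not damaged. What is damaged is any SAE count that the trial gives.

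A reader might infer more than the text supports:

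- **That serious events go unreported or are lost.** They do not. The adverse event record has no expectedness condition, and complications are collected as an outcome.
- **That a harm confined to one arm would reach nobody outside the team.** The internal committee meets at least monthly and discusses adverse events ({5d}). Section {22} adds review by treating teams described as outside the investigative team. The ethics board may access the data ({21a}), and auditing is independent of the investigators ({23}). None of these is an independent monitoring committee, but the absolute claim fails. The lack of such a committee and the timing of the interim analysis are separate matters.
- **That exempting tibial fracture is an error.** Exempting foreseen surgical complications from expedited reporting is a legitimate choice. Both arms have a reamed tibial tunnel, and the link to the tape arm's extra hole is inference.

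**Conclusion.** The section contradicts itself and is wrong as written. The definition, the rule for all SAEs and the exemption of expected SAEs cannot all hold. Taken literally, a serious listed complication is not an SAE and leaves the SAE count. On the other reading it is an SAE that is withheld from the ethics board, against the unqualified 72 h rule.

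The consequence is limited to misclassified events, inconsistent SAE counts and an unclear reporting duty. It does not extend to missing data or to a biased primary or complication analysis. The size cannot be stated as a number, because the protocol gives no complication rates; it covers every listed event that meets a seriousness criterion. The conclusion assumes that the article reproduces the operative wording of the protocol. It deserves correction because it concerns a safety rule and costs almost nothing to put right.

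**What to change.** 1. Delete the words *and unexpected*, so that seriousness alone defines an SAE.
2. Record expectedness for each SAE as a separate attribute that affects only expedited reporting to the ethics board.
3. Qualify the 72 h sentence so that it agrees with the exemption that follows it.
4. Report all SAEs by arm, whether or not expected.

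As a matter of judgement and not of correction, the sponsor and the ethics board may wish to confirm whether tibial fracture should stay on the exempt list, since only the tape arm has the added tibial anchor hole.

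Cost: a minor protocol amendment with ethics approval and a registry update, and slightly higher SAE counts. SAEs already classified since recruitment began would need one check against the revised definition.

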### Frequency and plans for auditing trial conduct {23}

Auditing of trial conduct will be performed at a frequency and depth as determined by the local ethics board, independent of investigators and research team.

### Plans for communicating important protocol amendments to relevant parties (e.g. trial participants, ethical committees) {25}

All modifications to study protocols, following approval with the local ethics board, will be documented as amendments in the ANZ clinical trial registry. All participants having previously signed consent forms prior to change in protocol will be notified by email including the detail of the change and its impact on them and offered an opportunity to review a new written consent. If the change will not impact the participants’ involvement in the study, a change in the statistical methods, or a reduction in the frequency of recording of SAEs, or a change in study personnel, as an example, would not impact the participants’ involvement in the trial and thus they will not be notified of these changes.

### Dissemination plans {31a}

By signing the consent form, the participants give their permission to allow the de-identified data generated by this research to be shared/discussed with the local institutional orthopaedic unit and those working within it. Information may be used in publication in peer-reviewed medical journals. The results may also be presented at relevant national or international meetings and conferences. The information from this study will be disseminated within presentations or publications related to the present study, or within research related to this study.

## Discussion

This manuscript reports on the methodological design of the STACLR trial (Suture Tape Augmentation of Anterior Cruciate Ligament Reconstruction), the first randomised design prospective trial comparing suture tape-augmented ACL reconstruction to standard ACL reconstruction in adult patients. In this study, 2-year objective knee laxity, subjective patient-reported outcomes, complications and return to sport rates will be compared in patient treated with tape-augmented ACL reconstruction to those without. The hypothesis of the present study is that suture tape augmentation of ACL reconstruction will result in reduced side-to-side anterior tibial laxity at 2 years post-operative. Secondary hypotheses include an improvement in PROMs and equivalent complication profiles in tape-augmented grafts.

There are several biomechanical studies comparing tape-augmented reconstruction to standard technique, whilst several animal studies and a scattering of retrospective nonrandomised clinical studies exist, all of which provide an established concept and lay the platform for future research. The most devastating complication of ACL reconstruction may be graft failure; however, owing to the sample size demanded, the present study will not feasibly investigate this, and it is important to note this when interpreting results. In a retrospective cohort study of tape augmentation in ACL reconstruction, Parkes et al. [28] in a post hoc analysis reported a sample size of 1290 to adequately power for graft failure. Nevertheless, on principle, the action of tape augmentation will be to increase the biomechanical strength of the graft, a property that has been established by author groups including Noonan et al. [23] and Lai et al. [54], where tape-augmented grafts have higher load to failure and reduced elongation under cyclic loading. It follows that this may result in reduced laxity in post-operative knees compared with the standard ACL technique. Therefore, the role of tape augmentation in increasing biomechanical strength is to protect the graft during maturation and protect those grafts at higher risk of failure. Observed reduced knee laxity post-operatively is a well-utilised measure in evaluating the return of anteroposterior stability after ACL reconstruction [19–22]. Notably, early laxity has been associated with poor outcomes including increased risk of graft failure, reduced length of athletic career, permanently increased knee laxity and lower return to function scores [55]. Therefore, the use of an arthrometric measure, namely the GNRB anteroposterior laxity (selected on the basis of its purported superiority over the KT-1000), is an efficient method of assessing the efficacy of tape-augmentation in achieving its biomechanical goal in an achievable sample size.

Given the previous pitfalls of synthetic graft augmentation [11], skeptics of the technique may cite stress shielding or synovial complications such as sterile effusion as drawbacks to the approach. Animal studies, however, have evidence that despite the biomechanical protection of cyclic elongation, histological evidence of graft remodeling occurs [24, 26], signifying that with the appropriate tensioning of the tape in full extension, stress shielding may be avoided. Similarly, Smith et al. 29 have reported equivalent rates of synovitis and ongoing effusion in tape-augmented and non-augmented canine knees at 6 months. These early findings purporting reduced complication profiles observed in other synthetic graft models establish the need for further, prospective clinical research. This study aims to address some of the above outstanding questions remaining regarding suture tape augmentation of ACL reconstruction.

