#### Secondary outcomes

Secondary outcomes are fourfold and will include (i) PROMs, (ii) return to sport rates, (iii) complications and (iv) examination findings.i)PROMs will be recorded preoperatively and post-operatively at 6 weeks, 3 months, 12 months and 24 months. PROMs collected will include the following:EQ5D-5L: The EuroQol EQ-5D-5L is a validated, generic, self-reported outcome measure covering five health domains that are used to facilitate the calculation of quality-adjusted life years (QALYs) in health economic evaluations. The original EQ-5D questionnaire contained three response options within each of five health domains (mobility, self-care, usual activities, pain/discomfort and anxiety/depression) [33]. More recently, the EQ-5D-5 L has been developed to overcome problems with ceiling effects and to improve sensitivity [43]. The 5 L version consists of the same five domains as the original but with five response options.The International Knee Documentation Committee (IKDC) score: The IKDC is a knee-specific patient outcome questionnaire often used after ACL reconstruction [31]. It is a subjective tool that provides an overall patient score (0–100), often interpreted as a measure of function, where higher scores represent a greater function. It aims to address three categories: symptoms, activity and overall function, and has shown adequate test-retest reliability and good construct validity in patients with issues at the knee [44].Knee injury and Osteoarthritis Outcome Score Quality of Life sub-scale (KOOS-QOL): This subscale is a 4-item questionnaire designed to evaluate the knee-specific quality of life, has been utilised among ACL surgical trials [30] and has been established to have validity, responsiveness and reliability in patients undergoing ACLR [45].ACL return to sport index (ACL-RSI): Psychological readiness to return to sport will be evaluated with the ACL-RSI. It is a 12-point questionnaire validated to evaluate a patient’s confidence and readiness to return to sport [34] and exhibits high internal validity and structural consistency [46]. Given the theoretical increased stability offered by suture tape augmentation, particularly in the early rehabilitative period, it follows that patients treated with this may experience improved perception of knee function and subsequent confidence in rehabilitation and sporting activity across the early postoperative period.Self-reported pain: We will record postoperative pain levels and long-term knee pain scores utilising 10-point visual analogue scale pain scores (VAS) where 0 is no pain and 10 is the worst pain imaginable.ii)Complications:We will record complications and adverse events including wound complications, infection rates, return to surgery, e.g. meniscal tears, graft failure, contralateral knee ACL rupture, residual effusion, rates of symptomatic arthrofibrosis of the knee and second look arthroscopy findings and the rates of sterile effusion. These will be recorded upon review of each patient’s medical record at 2 years.iii)Return to sport and activity:Return to sport and activity will be assessed via a self-reported questionnaire delivered concomitantly with PROMs preoperatively and post-operatively at 6 weeks, 3 months, 12 months and 24 months. Return to activity will be evaluated through the Marx activity scale, a four-item activity rating scale which has been shown to have excellent retest reliability in patients with knee injuries [32]. Participants will be asked to record on a scale of 0–4 how often they are able to perform each of running, cutting, deceleration and pivoting in their most active state across the preceding 12 months. A maximum score is 16 points. Participants will also be asked about their dichotomous return to sport status, their expectations regarding timing of return to sport, return to preinjury level of sport and the time postoperatively to return to sporting activity. These questions, along with the full set of pre-operative and post-operative PROMS, are included in Additional file 1.iv)Examination findingsExamination findings will be taken preoperatively at examination under anaesthesia and post-operatively at 6 weeks, 3 months and 12 months. Examination findings including the range of motion (ROM), the presence of knee effusion, Lachmans, pivot shift and anterior drawer testing will be recorded. All assessments will be undertaken by lead surgeons S.T, L.B.

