## Statistical methods

### Statistical methods for primary and secondary outcomes {20a}

Side-to-side difference in anterior tibial translation (the primary outcome), overall ACL-RSI, EQ5D-5L, Marx activity scales, IKDC and KOOS-QOL will be calculated as means, with measures of dispersion reported as standard deviation. Differences between groups will be reported as mean differences, with dispersion reported with confidence intervals. Data normality will be assessed with the Shapiro-Wilk test for continuous parametric assessment. Between-group comparisons, such as the primary outcome of mean difference in GNRB anteroposterior laxity at 2 years, will be assessed with independent samples *t*-tests. If data is found to be non-parametric in distribution, the Wilcoxon rank sum test will be utilised. Comparison of two dichotomous variables, such as return to sport rates and complication rates, will be performed with Fischer’s exact test. Repeated measures such as GNRB measures and mean PROMs will be assessed using mixed effects linear analysis. All tests are two-sided. A *p* value of <0.05 will be considered the cut-off for statistical significance.

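### Equivalent complication profiles are hypothesised, but the only stated analysis of complication rates is a test of difference with no equivalence margin, which cannot support that hypothesis

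*Protocol article*

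**What the plan says.** The opening paragraph of the Discussion gives the trial's hypotheses. After the laxity hypothesis it adds: "Secondary hypotheses include an improvement in PROMs and equivalent complication profiles in tape-augmented grafts".

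Statistical methods {20a} states how such outcomes are analysed: "Comparison of two dichotomous variables, such as return to sport rates and complication rates, will be performed with Fischer’s exact test". It adds "All tests are two-sided" and a p "value of <0.05 will be considered the cut-off for statistical significance". Confidence intervals are mentioned there only together with mean differences. No equivalence or non-inferiority test is named, and no margin appears anywhere in the document.

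The outcome is broad. Under Secondary outcomes: "We will record complications and adverse events including wound complications, infection rates, return to surgery", followed by graft failure, contralateral rupture, residual and sterile effusion, arthrofibrosis and second-look findings. These are collected by record review at 2 years.

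Trial design {8} describes a superiority trial, and Sample size {14} is based on laxity and IKDC. On graft failure, the Discussion says that "owing to the sample size demanded, the present study will not feasibly investigate this" and asks readers to bear this in mind. It says nothing similar about the other complications.

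**The concern.** Fisher's exact test takes no difference as its null hypothesis. A significant result would count against "equivalent complication profiles in tape-augmented grafts". A non-significant result leaves the hypothesis standing but is not evidence for it. The document therefore pairs a hypothesis with a test that has no outcome able to support it. Both items are stated, so this is a mismatch in the text and not detail left to an analysis plan.

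What is at stake is the safety conclusion. The Background reports persistent effusion and synovitis with earlier synthetic devices, and the Discussion says that critics may raise sterile effusion against this technique. If a non-significant p-value were set beside a pre-stated equivalence hypothesis, readers could take it as randomised evidence of similar safety when the data are compatible with a material increase.

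**Working it through.** **Inputs from the protocol.** 66 randomised 1:1, so 33 per arm; two-sided Fisher's exact test; cut-off p<0.05; 24 per group as the target before dropout.

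**Assumed inputs.** The document gives no complication rates and no margin. The rates and margins below are assumptions, shown as a range.

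**The plan's own figure.** There is no power or sample size for complications. The IKDC calculation reproduces: d = 18/√((17² + 25²)/2) = 18/21.4 = 0.842, which needs 23.1, rounded up to 24 per group (power 81%). The sizing therefore rests on continuous outcomes and says nothing about event rates.

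**Step 1: power of the stated test.** Exact power = Σ Bin(x; n, p₁) · Bin(y; n, p₂), summed over all pairs (x, y) with two-sided Fisher p<0.05.

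| True rates | Power, 33 per arm | Non-significant, 33 per arm | Power, 24 per arm |
|---|---|---|---|
| 5% vs 5% | 0.2% | 99.8% | 0.4% |
| 5% vs 10% | 2.5% | 97.5% | 2.8% |
| 5% vs 15% | 11.9% | 88.1% | 10.6% |
| 5% vs 20% | 29.3% | 70.7% | 23.7% |
| 5% vs 30% | 70.1% | 29.9% | 56.0% |
| 10% vs 20% | 11.5% | 88.5% | 9.7% |
| 10% vs 30% | 42.1% | 57.9% | 31.4% |

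Non-significance is almost as likely when a 5% rate doubles (97.5%) as when the arms are equal (99.8%). Observing it therefore barely separates the two.

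**Step 2: counts needed for significance, 33 per arm.** With no events in one arm and k in the other, two-sided p = 2·C(33,k)/C(66,k).
- k = 5: 2 × 237,336/8,936,928 = 0.053.
- k = 6: 2 × 1,107,568/90,858,768 = 0.024.

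So 0/33 against 5/33 is not significant, and 6/33 (18%) is needed. Against 1/33, the other arm needs 8/33 (24%).

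**Step 3: what the data could exclude.** The Newcombe interval is built from the Wilson limits (l, u) of each proportion. For 2/33, p = 0.0606, l = 0.0168 and u = 0.1961. With equal counts the half-width is √((p − l)² + (u − p)²) = √(0.0438² + 0.1355²) = 0.142, or ±14.2 points. The same method gives ±12.5 points for 1 vs 1 and ±15.7 for 3 vs 3. With 1/33 vs 5/33, p = 0.20 and the 95% interval runs from about −3 to +28 points.

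**Step 4: would a formal equivalence test be possible at this size?** For two one-sided tests at 5%, 80% power and equal true rates p, a normal approximation gives n per arm = 2p(1 − p)(1.645 + 1.282)²/margin². At p = 5% this is 0.095 × 8.56/margin²: 82 per arm for a 10-point margin, 37 for 15 points and 21 for 20 points. At p = 10% the figures are 155, 69 and 39. With 33 per arm, the approximate power at p = 5% is 17%, 75% and 96% for margins of 10, 15 and 20 points. The approximation is rough, since 5% of 33 is fewer than two expected events per arm.

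**The case against.** The strongest reply is that the protocol never says a p-value above 0.05 will be taken as equivalence. A reader might infer that equivalence will be declared on a non-significant test, but {20a} says only that the rates will be compared. That inference is about future reporting and is not a planned rule.

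Second, the word appears as a trial hypothesis only once, in the Discussion. Secondary objectives speaks only of comparing complication rates, the trial is framed as superiority, and the article elsewhere uses equivalent loosely for earlier findings. An ordinary sense of similar is plausible.

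Third, the authors already show caution on sample size, citing 1290 patients as the number needed for graft failure.

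Fourth, two stronger statements are tempting and fail. One is that the trial could report equal safety however much the tape raised complications: at 5% vs 30%, power is about 70%. The other is that 66 patients can never show equivalence: a margin of 15 to 20 points with a rate near 5% would come close to or exceed 80% power.

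Fifth, risk differences with intervals for each complication are detail often left to an analysis plan, so their absence alone is no finding.

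All five limit the point, but none removes it. The sentence is presented as a hypothesis, the one test named cannot support it, no margin is given, and the caution stops at graft failure.

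**Conclusion.** The mismatch between the Discussion and {20a} is real and narrow. The logical part needs no assumption: a non-significant test of difference does not show equivalence at any sample size. The quantitative part rests on assumed event rates, with 33 per arm as the most favourable case. On that basis a doubling or tripling of a 5% rate would be non-significant about 97.5% or 88% of the time, and a fourfold rise about 71%. Identical low counts would still leave roughly ±12 to ±16 points of uncertainty. Severity is minor: the outcome is secondary, and the primary analysis, sample size and conduct are unaffected.

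**What to change.** Make three edits:

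1. In the Discussion, replace the equivalence hypothesis with a statement that complication rates will be estimated and compared between arms, with no claim of equivalence.
2. In Statistical methods {20a}, state that complication rates will be reported as risk differences with 95% confidence intervals (for example Newcombe), alongside Fisher's p.
3. Extend the Discussion's caution from graft failure to all complications, stating that a non-significant difference will not be interpreted as equivalence.

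If the sponsor wants to keep an equivalence hypothesis, it needs a margin justified in advance, a matching test and a plain statement of the power available.

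The cost is wording and one extra column in the complications table. No additional data, patients or procedures are needed.
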